**Nail clippings for selenium**									
	Toenails	x	x	x		x	x		x
	Fingernails		x			x			x

^a^Iodine status: testing thyroglobulin and antithyroglobulin.

^b^Selenium status: testing plasma selenium.

^c^Iron status: testing hemoglobin, serum ferritin, soluble transferrin receptors, and C-reactive protein.

^d^Thyroid function: testing serum free triiodothyronine, free thyroxine, thyroid stimulating hormone, and antithyroid peroxidase.

### Statistical Analysis

Statistical analysis will be performed using SPSS Statistics version 23. The Shapiro-Wilk test will be used to test for data normality. Nonparametric data will be expressed as median (25th, 75th percentile), and parametric data will be expressed as mean and standard deviation. Bivariate correlations will be tested using the nonparametric Spearman 𝜌 correlation coefficient. Repeated-measures analysis of variance will be used to calculate continuous variables between groups. Nonparametric Mann-Whitney *U* test (2-tailed) will be used to examine iodine intake and status between supplement users and nonusers. Multiple regression models analysis will be used to determine the associations between iodine, selenium, iron status, and thyroid function, as well as considering confounding factors. Multivariate analysis will be used to examine possible associations between women’s selenium status, thyroid function, and postnatal depression and infant first year neurodevelopment.

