## Methods

### Study Design and Overview

The Mother and Infant Nutrition Investigation (MINI) study is an observational longitudinal cohort study spanning the first year postpartum. It was approved by the Health and Disability Ethics Committee (15/NTA/172) in December 2015. The study’s ethics approval was registered with the Royal New Zealand Plunket Ethics Committee in June 2016. The MidCentral District Health Board in New Zealand also approved the study. The study was registered with the Australian New Zealand Clinical Trials Registry [ACTRN12615001028594].

The study is being conducted in the Human Nutrition Research Unit at Massey University, Palmerston North, New Zealand. The first study visit for participants is at approximately 3 months postpartum, and follow-up assessments take place at 6 months and 12 months postpartum (Multimedia Appendix 1).

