### Selection Criteria

The target population for the study was healthy breastfeeding women aged over 16 years who had birthed a healthy term singleton infant 3 months prior. Women were excluded if they developed significant health problems, such as metabolic disease or cancer. Women were excluded if they had been diagnosed or treated at any time for hyperthyroidism or hypothyroidism. Participants were required to live within or near the local Palmerston North area and be able to attend Massey University for scheduled study visits. Women of any ethnic and socioeconomic status were eligible.

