### Sample Size Calculation

The main outcome measure was iodine excreted per day, and the sample size was calculated using G*Power 3.1 (Heinrich Heine University) based on data (mean and standard deviation) from a preliminary study of breastfeeding women [24]. Calculation used 1-way analysis of variance with two groups (95% power, 𝛼=.05, 2-tailed) and three repeat measures; 80 participants were needed, using expected mean daily urine iodine concentrations of 140 and 100 µg/d for iodine supplement users and nonusers, respectively, and a standard deviation of 60.

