#### Biomarker Analysis

During each study visit, spot urine samples from each participating woman and her infant were collected to assess iodine, selenium, and creatinine excretion. All maternal spot urine samples were collected in the morning and immediately frozen and stored at –20℃. Infant urine was collected using a 100 mL pediatric urine bag placed inside the diaper and checked every 10 minutes. The collected urine was frozen and stored at –20℃ for later analysis. Spot urine samples can be used to estimate iodine status of a population but not for individual iodine deficiency diagnosis [47]. It was not possible to estimate dietary iodine and selenium intake for lactating women via urine as we were unable to determine the daily loss of selenium from breast milk. As creatinine output is relatively constant, the adjusted iodine/creatinine ratio (µg iodine per g creatinine) can be used as a proxy measure of iodine excretion [48].

Lactating women were asked to provide a breast milk sample (approximately 30 to 50 mL) at each visit using an Allegro electric breast pump (Unimom NZ) if required. All breast milk samples were collected before noon on the study visit day, and timing of breast milk collection was not standardized. Breast milk samples were analyzed for iodine and selenium concentration, allowing for estimations of infant intake of iodine and selenium based on 750 mL/d of milk production [49].

Iodine and selenium concentration in both urine and breast milk samples were determined by an accredited commercial laboratory (Hill Laboratories) using inductively coupled plasma mass spectrometry (ICP-MS) [50]. Quality control procedures included analysis of blanks, analytical repeats, and certified reference material to ensure accuracy and precision. The Massey University Nutrition Laboratory measured creatinine using the Jaffe method in a Flexor E (Vital Scientific) biochemistry analyzer.

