**Breast milk (if available)**									
	Iodine	x		x			x		
	Selenium	x		x			x		

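### Repeated-measures ANOVA, in its conventional form, uses only women with a value at every visit analysed; for milk that would select on breastfeeding duration

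*Protocol article*

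**What the plan says.** The Statistical Analysis section of the protocol article names one method for repeated continuous outcomes: "Repeated-measures analysis of variance will be used to calculate continuous variables between groups". It does not list the outcomes concerned. The software is fixed ("Statistical analysis will be performed using SPSS Statistics version 23"), but the procedure within it is not. The same section gives the comparison of iodine intake and status by supplement use to a Mann-Whitney *U* "test (2-tailed) will be used to examine iodine intake and status between supplement users and nonusers". It also plans Spearman correlations and multiple regression.

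The Sample Size Calculation section assumes two groups with "95% power, 𝛼=.05, 2-tailed) and three repeat measures" and arrives at 80 participants for urinary iodine. The Results section reports 91 women-infant pairs enrolled.

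On who can contribute values, the Selection Criteria require "healthy breastfeeding women aged over 16 years who had birthed a healthy term singleton infant 3 months prior", and no requirement to continue breastfeeding is stated. Under Study Design and Overview, "follow-up assessments take place at 6 months and 12 months postpartum". The Biomarker Analysis section says "Lactating women were asked to provide a breast milk sample" at each visit, and Table 2 labels the row "Breast milk (if available". Maternal and infant spot urine are collected at all three visits.

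**The concern.** Conventional repeated-measures ANOVA works on a complete row per woman. A woman who lacks one of the visits analysed leaves the analysis altogether, along with the values she did provide.

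For urine, one missed visit or one failed infant collection is enough. For milk the problem is structural. A woman who weans before 12 months cannot have a third value, so a three-visit analysis of milk iodine or selenium would retain only those who gave milk at 3, 6 and 12 months. That group is narrower than the women still lactating at 12 months, since a missed earlier sample also excludes. It differs from the enrolled population, which is defined by breastfeeding at about 3 months. If continued breastfeeding is related to supplement use or mineral status, the longitudinal comparison could be biased as well as less precise.

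**Working it through.** **Reproducing the plan's figure.** Inputs from the Sample Size Calculation: means 140 and 100, SD 60, two groups, m = 3 measures, alpha 0.05 two-tailed, power 0.95. Not stated and assumed here: equal groups and a within-woman correlation rho.

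- Effect size: f = (140 − 100)/(2 × 60) = 0.333.
- Between-group F test with 1 and N − 2 degrees of freedom, noncentrality λ = f² × N × m / (1 + (m − 1) × rho).
- At N = 80, rho = 0.5: λ = 0.1111 × 80 × 3 / 2 = 13.33, power 0.950.

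The stated 80 is therefore reproduced with rho = 0.5. It presumes three values per woman. A single measure per woman would need 118 to 120 by the same inputs.

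**Power for urine by number of complete women** (same formula, rho = 0.5):

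| Complete women | Loss from 91 | λ | Power |
|---|---|---|---|
| 80 | 11 (12%) | 13.33 | 0.950 |
| 73 | 18 (20%) | 12.17 | 0.931 |
| 60 | 31 (34%) | 10.00 | 0.875 |
| 50 | 41 (45%) | 8.33 | 0.81 |

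The result depends on rho: at 60 complete women, power is 0.94, 0.875 or 0.81 for rho = 0.3, 0.5 or 0.7.

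**Women kept in a three-visit milk analysis.** The article gives no share with milk at all three visits, so a range is assumed: 70% of 91 is 64 women, 50% is 46 and 30% is 27.

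**Samples unused by that analysis.** Assume milk from all 91 women at visit 1 and no return to milk once it is absent. Samples collected = 91 × (1 + s2 + s3); samples used = 91 × 3 × s3, where s2 and s3 are the shares at visits 2 and 3.

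| s2, s3 | Share unused |
|---|---|
| 0.9, 0.7 | 1 − 2.1/2.6 = 19% |
| 0.8, 0.5 | 1 − 1.5/2.3 = 35% |
| 0.6, 0.3 | 1 − 0.9/1.9 = 53% |

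**Can selection bias the comparison?** A constructed simulation used 91 women, a true difference of 40, SD 60, rho 0.5 and 200 runs. Half the users were retained at random, and nonusers were more likely to be retained if their visit 1 value was high. On average about 46 women were complete. The complete-case difference averaged 17, and a mixed model on all available values averaged 40. This shows that bias is possible under such retention. It is not an estimate for this study.

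**The case against.** A reader might infer that the milk analysis is restricted to long-duration breastfeeders and that all other women's data are thrown away. The article does not support this. It never names milk as an outcome of the repeated-measures ANOVA, so the milk consequence is conditional on that use. The loss is also confined to this one analysis, because Mann-Whitney, Spearman and regression can all use visit 1 and 2 values from women who later wean or leave.

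A reader might also infer that the user versus nonuser comparison of iodine status as a whole would describe only complete cases. It would not, since that comparison is assigned to Mann-Whitney, which does not need three visits. What Mann-Whitney cannot do is model change over visits or within-woman correlation, so it does not replace the longitudinal analysis.

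A serious loss of power for urine is not shown either. Urine does not depend on lactation, 91 is 11 above the 80 required, and reaching 60 or 50 complete women would take a loss of 34% or 45%, which nothing in the article suggests. Milk has no power target at all.

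A short article may leave the handling of incomplete series to a fuller plan, and that silence is no fault. The point rests instead on the method the article does name.

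Finally, a mixed model is no complete answer for milk. Under missing at random it implicitly estimates means as if weaned women were still producing milk, and a within-woman trend among continuous breastfeeders is a legitimate target if labelled. This objection stands and shapes the fix.

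**Conclusion.** The point holds in conditional form and is worth acting on. The only repeated-measures method named is one whose conventional form requires a value at every visit analysed, and it suits these data poorly: mildly so for urine, structurally so for milk if milk is analysed this way. The sample size of 80 is not in error.

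The size is open. The remaining 64 to 27 women follow from assumed completeness of 70% to 30%, and the urine power figures (0.95 down to 0.81) rest on an assumed rho of 0.5 and equal groups. The direction is clear: fewer women, and for milk a group selected on breastfeeding duration. Whether the result would be biased depends on how weaning and dropout relate to supplement use and status, which the article does not tell us.

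**What to change.** Replace repeated-measures ANOVA with a linear mixed model for repeated measures, with visit, group, group-by-visit and within-woman correlation, on the log scale if values are skewed. Fit it to all available visits.

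For milk, report visit-specific estimates as applying to women lactating at that visit. Do not read the model's missing-at-random means as values for women who have weaned. If a within-woman trend is reported among women with all three samples, label it as such. Breastfeeding patterns are asked about at every visit, so these groups can be described.

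The cost is one changed procedure in the same software and a few sentences on the population each milk estimate refers to. No new data are needed, and the article reports results as still to come. The downside is reliance on missing at random for urine, which is a weaker assumption than complete-case analysis needs.

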## Results

Recruitment traversed the 19-month period between June 2016 and December 2017, and a sample of 91 women-infant pairs was enrolled (Figure 1). Data collection has been completed. Biological samples analysis, excluding nail clippings, is complete. Data analysis and presentation of the results will be available after 2020.

**Figure 1 figure1:**
[figure not shown]
Flow chart showing recruitment for the Mother and Infant Nutrition Investigation study.

## Discussion

### Summary

A unique aspect of this study is that it will investigate all three micronutrients responsible for adequate thyroid hormone synthesis concurrently, rather than each separately in isolation. This observational longitudinal cohort study will measure the iodine and selenium status of women repeatedly in their first year after birth, which provides an evaluation of their nutritional status. Iodine status among supplement users and nonusers will provide up-to-date data on this postpartum group in New Zealand around 8 years after government interventions. Results will explore whether maternal iodine and selenium status could be used as a proxy measure of infant status. It provides an opportunity to examine the association of maternal iodine and selenium with infant neurodevelopment during their first year. This study explores selenium status using both short-term and long-term measures in relation to neurodevelopment at 6 months and 12 months of age, which has not been reported previously. Furthermore, the study results will add preliminary data on iron status of women at 6 months postpartum.

Importantly, the study will investigate overall thyroid function of women at 6 months postpartum with respect to the risk of postnatal depression. Measurement of thyroid hormones, thyroid stimulating hormone, anti-TPO, Tg, and anti-Tg in serum as well as measuring thyroid gland volume via ultrasound will provide an overall picture of maternal thyroid function after giving birth. This is an opportune time to check thyroid status, especially as women with limited thyroidal reserve or iodine deficiency in pregnancy may develop postpartum thyroid dysfunction, one of the most common endocrine disorders women experience [6,58].

Additionally, there will be longitudinal assessment of mothers’ mental health via repeated screening by using the EPDS. The results may add to the literature in postpartum mental health status. Their offsprings’ growth and neurodevelopment will be followed during the first year after birth. The findings from this study have the potential to inform future public health policy and practice regarding postpartum women’s nutritional status and mental health together with infant health outcomes.

## Appendix

Multimedia Appendix 1 Flow chart showing stages of Mother and Infant Nutrition Investigation study.

## Abbreviations

Anti-Tg: antithyroglobulin antibodies
Anti-TPO: antithyroid peroxidase
ASQ: Ages and Stages Questionnaire
CMIA: chemiluminescent microparticle immunoassay
EPDS: Edinburgh Postnatal Depression Scale
ICP-MS: inductively coupled plasma mass spectrometry
MINI: Mother and Infant Nutrition Investigation
T3: triiodothyronine
T4: thyroxine
Tg: thyroglobulin
